### Statistical analysis

All statistical analyses will be performed using the IBM SPSS Statistics version 20. The main analyses will be conducted on the intention-to-treat samples (all randomised participants, regardless of protocol adherence). Following current standards [27, 28], a linear mixed effects models approach with full information maximum likelihood estimation will be used. This approach has been recommended since it uses all available data and can handle missing data appropriately [118, 119]. The approach is based on the assumption that data are missing at random, and does not assume that missing data remain stable, as in the last-observation-carried-forward (LOCF) approach [119, 120]. Significance testing of dichotomous data such as diagnostic status will be conducted with chi-square tests. Calculations of within- and between-groups effect sizes (Cohen’s d) will be based on the pooled standard deviations. Regression analyses will be used to identify predictors of treatment outcome. Moderation and mediation analyses will be conducted with multiple regression models, using the PROCESS macro for SPSS [121], a computational technique that can compute both simple and complex moderation and mediation models. Effect sizes for significant effects will be indicated by Cohen’s f.

Consistent with CONSORT [77] and SPIRIT [78] recommendations we mention our intention to perform secondary analyses for minimal treatment users, defined as participants that complete at least 5 of the recommended modules, have at least 3 of the available guidance sessions (this is available only for the Skype-guided group) and use the intervention program for at least 80 min. This definition is based on the specific of our intervention program and the criteria used in other studies [27, 119].

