#### Therapists

Three licensed psychotherapists with formal training in cognitive-behavioral therapy and a minimum of 3 years of clinical experience work with the participants allocated in the first treatment group. They have also participated in a 3 months blended course (3 face to face meetings plus online learning) prior to this study and were instructed in using the PAXonline platform and delivering CBT interventions online. The guidance will be delivered according to a standard treatment protocol, but it will also be personalized according to each participant’s need. During the study, the team meets once a month for discussions and the main researcher is available for contact at any time.

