### Randomization

Participants who return the informed consent and meet all the required criteria are randomly allocated to one of the three conditions (1:1:1 allocation ratio). The randomization process is done by a software that was developed to implement a minimization algorithm [112], that assures a balanced randomization between groups with respect to certain predefined prognostic (stratification) factors. In this study, two stratification factors have been considered: SEVERITY (3 levels according to PDSS-SR screening scores; level 1: 6 to 13 points; level 2: 14 to 20 points; level 3: 21 to 28 point) and CHRONICITY (2 levels; more or less than 6 months since the beginning of PD) of panic disorder. The minimization method has been shown to outperform simple randomization in achieving balanced groups [113] and its use in clinical trials has been previously recommended as a better option than other randomization methods (e.g. [113–115]). Before each allocation, the algorithm computes an imbalance score for the three available treatments, taking stratification factors levels into account. The treatment with the lowest imbalance score is then given preference when assigning treatments, but the allocation probability varies for each patient, depending on the actual level of imbalance [116]. This method is preferred because it avoids the deterministic allocation of pure minimization [117]. The allocation is done by an independent researcher and is concealed, i.e. patients and researchers have no knowledge and no control over the allocation of participants when they randomize a participant with the computer program.

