### Sample size

The effect sizes reported between guided and unguided interventions are quite heterogeneous with small to medium Cohen’s d size effects between 0.27 [64] and .42 [14]. Taking into consideration that, in most part, the guidance in previous studies was in fact low-intensity guidance, and that more support from a therapist yields larger effects [21, 62, 63], we expect an effect size of 0.5 (Cohen’s d) between guided and unguided treatment for PD. Based on this effect size, a power of 0.80, and an alpha level of 0.05, we would need 51 subjects in each condition. This recommended sample size has been increased to accommodate an attrition rate of 20 %. Thus, the study aims to achieve a sample of 192 participants.

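### Diagnostic status, a primary outcome, is tested with an unadjusted chi-square although allocation is minimised on severity and chronicity: valid, but mildly conservative and somewhat less powerful than an adjusted analysis if those factors are prognostic

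*Protocol article*

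**What the plan says.** The Primary outcomes section names two primary outcomes: diagnostic status at post-assessment and panic symptoms on the PDSS-SR. For the first, the Statistical analysis section states: "Significance testing of dichotomous data such as diagnostic status will be conducted with chi-square tests". The Diagnostic interview section adds that a missing post-treatment interview counts as still meeting criteria, so all randomised participants enter this test.

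The Randomization section describes a minimisation algorithm with a random element, in which "two stratification factors have been considered: SEVERITY (3 levels according to PDSS-SR screening scores", plus chronicity in two levels split at 6 months. It describes these as prognostic factors. Participants are "randomly allocated to one of the three conditions (1:1:1 allocation ratio").

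For PDSS-SR the Statistical analysis section names a linear mixed model with full information maximum likelihood and does not list its terms.

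The guided arm is served by "Three licensed psychotherapists with formal training in cognitive-behavioral therapy" (Therapists). The Sample size section gives its calculation in Cohen's d for guided versus unguided treatment and does not mention clustering by therapist.

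**The concern.** The design and the stated test do not match. The trial balances the arms on two variables because it regards them as prognostic, and then tests a primary outcome in a way that cannot use them. Balancing on a prognostic variable makes the arms more alike than simple randomisation would. An unadjusted test still uses a variance that includes the between-level differences, so that variance is somewhat too large. The consequences are a type I error below the nominal level and lower power; false positives are not inflated.

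Severity is also close to this outcome. The protocol says a PDSS-SR cut-off of six may separate presence from absence of current panic disorder, and the severity levels are bands of the same scale starting at six.

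A lesser, separate matter affects only comparisons with the guided arm. If outcomes differ between the three therapists, participants who share a therapist are correlated, and the sample size makes no allowance for this.

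**Working it through.** **Plan's own figures.** The inputs come from the Sample size section. On the effect it says: "we expect an effect size of 0.5 (Cohen’s d) between guided and unguided treatment for PD". On error rates and the resulting number per arm it says: "a power of 0.80, and an alpha level of 0.05, we would need 51 subjects in each condition". Attrition is put at 20% and the total at 192.

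- n per arm = 2(z_alpha + z_beta)^2 / d^2.
- One-sided 0.05: 2(1.645 + 0.842)^2 / 0.25 = 49.5, so 50; the exact t calculation gives 51.
- Two-sided 0.05: 2(1.960 + 0.842)^2 / 0.25 = 62.8, so 63; the exact t gives 64.
- Attrition: 51 / 0.8 = 63.75, so 64 per arm, and 3 x 64 = 192.

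The stated 51 and 192 therefore reproduce with a one-sided alpha, for independent participants and a continuous outcome. Sidedness is not stated and is a separate matter. No power is stated for diagnostic status, so there is no plan figure for the chi-square test to reproduce. Because missing interviews are counted as diagnosed, about 64 per arm enter that test.

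**Chi-square against adjusted logistic regression, by strength of the factors.** I simulated three-arm minimisation on severity and chronicity, N = 192, with one two-arm contrast tested two-sided at 0.05 and no missing interviews. Assumptions not in the documents: biased coin 0.8; severity levels 45/40/15%; 70% in the more chronic group; treatment log-odds 1.0. There were 2,500 null and 1,500 alternative runs, so simulation error is about ±0.009 on type I error and ±0.02 on power.

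| Log-odds per severity level / for chronicity | Type I error: chi-square, adjusted | Power: chi-square, adjusted |
|---|---|---|
| 0 / 0 | 0.044, 0.046 | 0.77, 0.77 |
| 0.7 / 0.5 | 0.051, 0.060 | 0.73, 0.75 |
| 1.2 / 1.0 | 0.025, 0.044 | 0.64, 0.71 |

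**By baseline-outcome correlation r, including the missing-data rule.** Three-arm minimisation, 64 per arm, r = 0.3 to 0.5 (assumed):

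- No missing interviews: chi-square type I error is about 0.033 to 0.050 across these settings; adjustment gains about 4 to 7 power points.
- 20% missing (the protocol's attrition rate) and counted as diagnosed: the gain is about 1 to 3 points. A further set of 3,000 runs, with an assumed random element of 0.3 in the minimisation, gave power 0.45 against 0.46 at r = 0.3 and 0.45 against 0.49 at r = 0.5. Type I error was 0.048 against 0.052 and 0.042 against 0.053. With a simulation standard error of about 0.009 on power, this agrees with 1 to 3 points.

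The gain shrinks because participants imputed as diagnosed have an outcome unrelated to their baseline.

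**Therapists (supporting only).** At 51 per arm, shared equally, m = 51/3 = 17. Design effect in the guided arm = 1 + (17 - 1) x ICC. The standard error of guided versus unguided grows by sqrt((1 + design effect)/2). The ICC values are assumptions; the documents give none. Power is for d = 0.5.

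| ICC | Design effect | SE ratio | Two-sided type I error if ignored | One-sided power with the true SE |
|---|---|---|---|---|
| 0 | 1.00 | 1.000 | 0.050 | 0.81 |
| 0.01 | 1.16 | 1.039 | 0.059 | 0.78 |
| 0.02 | 1.32 | 1.077 | 0.069 | 0.76 |
| 0.05 | 1.80 | 1.183 | 0.098 | 0.69 |
| 0.10 | 2.60 | 1.342 | 0.144 | 0.59 |

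**The case against.** An unadjusted chi-square is simple and valid, and any error is on the safe side. With weak or moderately prognostic factors its type I error is close to nominal. The Background itself reports conflicting evidence on whether baseline severity predicts outcome. The missing-as-diagnosed rule removes much of the benefit of adjustment. Part of the apparent gain may also reflect the adjusted test's slightly higher rejection rate under the null (0.060 in the moderate case, near the limit of simulation error). All of this stands, and it limits the point to a modest efficiency gain. It does not remove the point: the test is fixed in the text for a primary outcome, the factors are already recorded, and adjusting costs almost nothing if they prove weak (0.77 against 0.77).

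A reader might also infer that the PDSS-SR mixed model ignores baseline or the minimisation factors. The article does not show this. It lists no model terms, as a condensed article commonly does not, and the pre-treatment score is ordinarily part of a repeated-measures model.

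On therapists, the random effects are likewise unlisted, so the article does not say that guided participants are treated as independent in the analysis. What it does show is a sample size with no allowance for clustering. Three therapists are too few to estimate a therapist variance well, and the contrast of unguided treatment with waiting list is unaffected.

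**Conclusion.** The point holds for diagnostic status only. The chi-square test is valid but mildly conservative, and it loses some power if severity and chronicity are prognostic: about 1 to 3 points under the protocol's missing-data rule with 20% missing, about 4 to 7 with none missing, and nothing if the factors do not predict outcome. These sizes rest on an assumed correlation of 0.3 to 0.5, 64 per arm, pairwise comparisons and an assumed random element in the minimisation.

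One might be tempted to conclude that the trial's p-values and intervals are miscalibrated in general. The documents do not support that. Ignoring the balancing factors and ignoring therapists act in opposite directions, each depends on a quantity the documents do not give, and the mixed-model terms are not shown. The therapist matter merits an optional supporting analysis. It is not a demonstrated error in the primary comparison.

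**What to change.** 1. Make the primary test of diagnostic status a logistic regression on arm, adjusted for severity level (or baseline PDSS-SR) and chronicity, with the form of the severity covariate chosen in advance. Report a standardised risk difference with confidence interval, so that the result remains a difference in proportions. Keep the chi-square test as a supporting result.
2. Optionally, for comparisons with the guided arm, report a supporting analysis that recalculates the standard error over an assumed ICC range such as 0.01 to 0.10, and state that inference refers to these three therapists.

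Both are changes of wording made before analysis. Severity, chronicity and baseline PDSS-SR are already collected, and the treating therapist should be known from delivery. Step 1 needs a little programming for the standardisation. Step 2 will be imprecise with three therapists, which is why it stands beside the primary result and does not replace it.

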## Discussion

The prevalence of mental health problems is very high and bears considerable suffering and burden worldwide. However, only a small percentage of the affected individuals reach out and receive treatment for their problems. There are many barriers at different levels, yet a viable solution to increase access to quality treatment resides in the possibilities provided by internet-based cognitive behavioral treatments. Although several ICBT programs have been tested with strong positive results and even integrated into regular health care, there are countries where validated internet-based interventions are yet to be developed. The present trial aims both to validate the overall efficacy of the first Romanian ICBT program for panic disorder, and to investigate aspects that are novel to ICBT, such as brief therapist guidance sessions via secured Skype.

There are still divergent results regarding the effect of therapist guidance in ICBT [18, 31, 56–58], and the efficacy of Skype-based (or equivalent) therapy sessions in ICBT have not been previously investigated. Thus, a central focus of our trial is to test the additive effect of therapeutic guidance via secured Skype in self-help ICBT programs. Specifically, the current study design allows us to assess the effect of the same self-help intervention modules in two treatment conditions: therapist guided via Skype vs. unguided self-directed intervention.

There is a general consensus that internet-based therapy can be efficient for many psychiatric conditions, but not all the patients benefit from it [44]. Thus, there is an increasing interest to describe the characteristics of the patients who would benefit the most from this type of interventions. Taking into consideration this issue, additional exploratory analyses of potential predictors, moderators or mediators will be made. Patients’ treatment expectations, personality traits (e.g. personal autonomy), and usability of the online treatment program could prove to be key factors of treatment adherence and outcome, especially in the unguided self-help treatment group.

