Several possible limitations should be noted. Firstly, the study sample size is large enough to reach our main research objectives, but will not permit us to perform detailed subgroup analyses. However, we expect to identify candidate predictors of treatment outcome that could be tested directly in future studies with larger samples. Secondly, the control group, for ethical reasons, will receive treatment in the second stage of the trial, thus the control group will not be available at follow-up. Furthermore, most of the recruitment will be made from the community, through advertisements in the media and on the study website, which could lead to a self-selected sample. Regarding the latter limitation, several findings from recent studies suggest that sampling bias may not affect the generalizability of internet-based trials. For example, Titov et al. [122] revealed that patients undergoing web-based treatments resemble national samples and present disorders as severe as those undergoing traditional psychotherapy. Another example is a recent study by Donkin et al. [123] on sampling bias in an internet-based clinical trial for depression. The authors revealed that out of 35 potentially biasing factors, only 4 were associated with consenting likelihood, accounting for limited variance in explaining participation, and none were associated with the primary outcomes. Future research will be required, nonetheless, to investigate whether the results from the PAXonline trial can be generalized to samples in regular mental health care settings.

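### Read literally, the plan gives Cohen's f for the exploratory predictor, moderator and mediator effects only when they are significant, which would select the reported values upwards (minor, exploratory reporting only)

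*Protocol article*

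**What the plan says.** The Statistical analysis section of the protocol article makes two separate commitments on effect sizes.

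- For group differences, "Calculations of within- and between-groups effect sizes" (Cohen's d) are to use pooled standard deviations. No significance condition is attached.
- Next come the exploratory models: "Regression analyses will be used to identify predictors of treatment outcome", and "Moderation and mediation analyses will be conducted with multiple regression models" using the PROCESS macro. The paragraph then closes with "Effect sizes for significant effects will be indicated by" Cohen's f.

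The Discussion describes the status and use of this work: "additional exploratory analyses of potential predictors, moderators or mediators will be made", and, among the limitations, "we expect to identify candidate predictors of treatment outcome that could be tested directly in future studies with larger samples".

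**The concern.** The f sentence comes straight after the predictor, moderator and mediator models, so its natural reading is that it governs them. It names significant effects and promises nothing for the others. The d commitment in the same paragraph has no such limit.

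A standardised effect that is shown only after passing a significance test is a selected estimate. When power is low, an effect passes mainly in samples where it happens to be overestimated, so the average reported value exceeds the truth. Candidates that fail the test have no f beside which the reported ones can be judged. The Background section itself notes few stable predictors and conflicting findings for adherence, severity and comorbidity. Selected effect sizes would make a new set of results harder to compare with that literature.

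**Working it through.** **The plan's own figures.** The plan gives no power, sample size or expected effect for these analyses, so there is no stated result to reproduce. Its sample numbers set the range of N. The Sample size section has 51 per arm before attrition, and 51 / (1 − 0.20) = 63.75, rounded up to 64; 3 × 64 = 192. I use:

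- N = 102 (two active arms of 51 completers, 2 × 51);
- N = 192 (all randomised participants).

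The cases N = 128 (2 × 64) and N = 153 (3 × 51) fall between these two.

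**Assumptions.** The Sample size section states "an alpha level of 0.05" without saying whether it is one- or two-sided; I take two-sided. Each test is of a single predictor. True correlations of 0.1, 0.14, 0.2 and 0.3 are assumed, because the document gives none.

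**Formulas.**

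- Fisher's z: z = atanh(r̂) is approximately normal with mean atanh(r) and standard error 1/√(N − 3).
- Cohen's f = |r̂| / √(1 − r̂²), which equals sinh|z|.
- An effect is significant when |z|·√(N − 3) > 1.96.

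**Smallest f that could be reported.**

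- N = 102: 1.96/√99 = 0.197, and sinh(0.197) = 0.198.
- N = 192: 1.96/√189 = 0.143, and sinh(0.143) = 0.143.

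**Mean f among significant results**, by simulation from the normal distribution of z:

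| True r | True f | Power, N = 102 | Mean reported f | Ratio | Power, N = 192 | Mean reported f | Ratio |
|---|---|---|---|---|---|---|---|
| 0.10 | 0.101 | 17% | 0.253 | 2.5 | 28% | 0.189 | 1.9 |
| 0.14 | 0.141 | 29% | 0.263 | 1.9 | 49% | 0.202 | 1.4 |
| 0.20 | 0.204 | 52% | 0.284 | 1.4 | 80% | 0.231 | 1.1 |
| 0.30 | 0.314 | 87% | 0.342 | 1.1 | 99% | 0.317 | 1.0 |

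**Moderators.** For a difference in standardised slopes between two arms of 51, with residual SD 1, the standard error is √(2/51) = 0.198. True differences of 0.2, 0.3 and 0.5 have power of about 17%, 33% and 71%. The mean significant estimate is about 2.5, 1.7 and 1.2 times the truth.

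**Without the filter.** Averaging f over all results at N = 102 gives ratios of 1.17, 1.06, 1.01 and 1.01 for the four correlations. The small excess at r = 0.1 arises because f has no sign. The rest of the inflation comes from the significance condition.

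**The case against.** The strongest reply is that the sentence can be read as naming the metric. The word 'only' does not appear, and nothing says that other effects will go unreported. The article is also condensed, and the layout of exploratory tables is commonly left to an analysis plan that is not shown.

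Part of this stands. The restriction is a literal reading, not a declared intention. Had the article been silent on confidence intervals or on the number of candidates, that silence would be no finding. But it is not silent on the condition: it writes significance into the commitment for f and leaves it out of the commitment for d a few sentences before.

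A reader might also infer more than the document supports:

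- **That all effect sizes are conditional on significance.** They are not; Cohen's d is promised without condition.
- **That null results will be hidden.** At most one standardised index is affected. Nothing says that coefficients, standard errors or p-values of non-significant terms will be withheld.
- **That later studies will be handed inflated effect sizes to plan on.** The Discussion passes on candidate predictors to be tested directly, not magnitudes for sample-size planning.
- **That the rule creates a high chance of a spurious finding.** If 10 to 20 independent null candidates were tested, the chance of at least one significant result would be 1 − 0.95^10 = 40% to 1 − 0.95^20 = 64%. That is a multiple-testing rate on an assumed count. It does not depend on which effect sizes are printed, and the fix below does not change it.

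**Conclusion.** The point holds as a minor one, confined to how exploratory effects are reported. Followed as written, the sentence yields a selected set of f values and none for null candidates.

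How far the reported values overstate the truth rests on the assumed true effect and on N. It runs from about 2.5 times (r = 0.1, N = 102) to almost nil (r = 0.3, N = 192), so it would be wrong to say that every reported f will be materially inflated. The figures also assume single-predictor, two-sided 5% tests. The efficacy comparisons are not affected.

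**What to change.** Replace the f sentence in the Statistical analysis section with:

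> Effect sizes (Cohen's f) with 95% confidence intervals will be reported for every predictor, moderator and mediator effect tested, whether or not significant, with the number of candidates tested.

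This removes the selection. The interval also shows when a small f is compatible with no effect, which matters because f is unsigned. The cost is one sentence now and longer supplementary tables later. It needs no new data and no change to the design or the models.
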